### 2.7. Blinding

As this will be a double-blind study, a third party not involved in the experiment will administer and supervise the blind strategies as follows:

(1) Participants will not be permitted to open the envelopes in the order in which they will be involved in the study. Assuming a tDCS model of modes A and B, the study implementer will not have any knowledge of what the stimuli represented.

(2) The A model represents an active stimulus, and the B model represents a sham stimulus. A third-party evaluator will evaluate the treatment results without information regarding the subgroup.

(3) The first non-blind method will be conducted until the applied mathematical analysis is completed to overcome subjective tendencies among the analysts during the data analysis process. After statistical analysis, a second non-blinded test will be conducted to determine the intervention group.

(4) Participants will be randomly asked whether they received an active or sham stimulus to ensure that they do not recognize the stimulation pattern.

### 2.8. Ethics issues

This study has been approved by the Ethics Committee of the First Affiliated Hospital of Nanchang University: Clinical Medicine Ethics Review [2015]043.

### 2.9. Dissemination plan

This study aims to investigate the possibility of conducting a multi-centered RCT to assess the effectiveness of tDCS in the treatment of PPD. Therefore, the objectives of the dissemination plan associated with this study are as follows: (1) offering insight for future studies to provide evidence for a multi-centered study examining the efficacy of tDCS in the treatment of PPD and (2) raising awareness and interest among the community and public regarding the potential possibility of this treatment approach in preventing unfavorable maternal and infant outcomes. This approach can facilitate the overcoming of hindrances to treatment satisfaction by ensuring that a clear and impartial message is delivered to potential treatment users, thereby encouraging effective and timely decisions regarding treatment. The group involved in this study is linked to clinical brain stimulation programs, and retraining on the use of tDCS procedures can be offered. Study findings will be presented in peer-reviewed publications to facilitate the rationality of our outcomes. Additionally, individuals suffering from PPD, as well as their families, will be informed of the outcomes in an encouraging and non-stigmatizing manner, ensuring that we facilitate the mass interest in participating in larger treatment trials and the subsequent adoption of this treatment approach.

### 2.10. Informed consent procedures

Participants will be provided with a clear explanation of the purpose, process, risks, and benefits of this study, and all questions asked by participants with the intention of confirming their understanding of the study, the risks and latent benefits of being involved in the study, and their privileges as study subjects will be answered before they sign the consent papers. Patients are required to sign an informed consent document before participating in the study. Informed consent should be obtained prior to any research evaluation or procedures, and before any private information is recorded. During the study period, participants will have an opportunity to agree to continue using the study protocol. We will also request that subjects invite their family and friends to participate in an initial discussion about the study so that all individuals involved in deciding whether to enroll in the study have adequate information. We will guarantee privacy protection of personal information.

### 2.11. Interventions

The intervention group will receive active tDCS, as well as clinical treatment and nursing care. The control group will receive sham tDCS as well as clinical treatment and nursing care. The treatment will be administered six times per week for 3 weeks. Regarding quality management, all the processes involving associated protocols, treatment approaches, and assessments will be standardized and conducted by the therapists participating in this study.

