## 2. Method

### 2.1. Study design

The RCT will involve recruiting patients with PPD for up to 1–2 years from professional postpartum psychological health projects in the Departments of Psychosomatic Medicine, Rehabilitation Medicine, Obstetrics, and Gynecology at the First Affiliated Hospital of Nanchang University. To recruit enough participants, leaflets and posters will be posted at the place of recruitment, and physicians will be informed about this study to assist in identifying qualified participants. The research coordinator conducted a baseline visit before the start of the active study to collect information on baseline demographics, to gain access to health services, and to gather baseline Montgomery-Asberg Depression Rating Scale (MADRS) measures.

In addition to the intervention, sham control will also be carried out within the Core Clinical Experiment at the first Affiliated Hospital of Nanchang University by well-trained researchers to guarantee proper supervision throughout the procedures. The active period of the experiment involving altogether 18 intervention or sham control sessions lasting for 20 min for approximately 3 weeks (6 days per week). The researchers who manage the session will record the date of every visit, the participant's blood pressure and heart rate, the starting and finishing times of sham tDCS, and interruptions, if any. All confounding factors (such as a previous history of depression, treatments, family history, etc.) will be analyzed. Outcome questionnaires will be collected from patients with PPD at three time points: before the procedures after enrollment (T1), 1 week after completing the procedures (T2), and 3 weeks after completing the procedures (T3). Follow-up questionnaires will be completed in person or by phone 8 weeks after completing the procedures. Patients will receive email updates concerning enrollment goals and the integrity of follow-up to help them to perceive the contributions that they made while participating in the study. Participants are then contacted with outcome information gathered and organized by professionally trained and experienced researchers. Personal outcome information is blind to the researchers, participants, and physicians who provided clinical treatment and care in the study group assignment.

The flow diagram of this study design is shown in Figure 1, and the evaluation of different time points is shown in Table 1.

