### 2.6. Randomization and allocation concealment

Following the informed consent process and the assortment of baseline information, individuals suffering from PPD who meet the eligibility criteria pertinent to this study will randomly receive active or sham tDCS. A study aide outside the confines of this study will present an assignment sequence using a randomized table of arranged blocks, and group distributions will be put into air-tight envelopes. The randomization identification numbers (RIDs) in the table will be stratified by the age of the newborn baby at enrollment to balance the gestational age of each group. Therefore, the first layer of RIDs will be distributed to participants who are <3 weeks into the postpartum period at the time of registration. The second layer of RIDs will be distributed to participants who are 3 weeks or more into the postpartum period. The experiment coordinator, while remaining blind to the group assignments, will select an envelope to include in the participants' chart. The experimenter will then open the envelope to ascertain the packet assignment, and program the tDCS device accordingly. The researchers will document the outcome measures objectively. The participants and researchers collecting maternal and infant clinical outcome data will also remain blind to the group distributions.

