#### 2.11.2. Active tDCS

Participants in the intervention group will receive active tDCS treatment for PPD. The anode of the electrode will be placed on the left dorsolateral prefrontal cortex (dlPFC), and the cathode on the upper edge of the right track. Based on a previous professional study, the current strength will be set at 2.0 mA (Vigod et al., 2019). The circular electrode area size will be set at 35 cm^2^ (5 × 7 cm). The duration of the treatment will be set at 20 min per session, once a day for 6 days each week (Figure 2A). The participants will be treated with tDCS only, and will not be simultaneously treated using other methodsI. The treatment will be performed in a neuromodulation room at a designated time by a designated therapist.

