### 3.3. Follow up

After the three-week treatment, an eight-week follow-up will be performed. The participants will be contacted by medical staff by phone or in person. Additionally, participants will be contacted every 2 weeks to document their medication and recovery. During the final week of the follow-up process (week 8 of post-intervention), the participants can be referred for a clinical evaluation to evaluate their prognosis and their status of disability.

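### Section 2.11 has the treating therapists conduct the assessments, which include the primary-outcome MADRS, while section 2.7 gives evaluation of results to a third-party evaluator without group information; both cannot be followed

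*Protocol article*

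**What the plan says.** All references are to the protocol article.

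- **2.11 Interventions**, in a sentence on quality management: "treatment approaches, and assessments will be standardized and conducted by the therapists participating in this study".
- **2.11.2 Active tDCS**: "The treatment will be performed in a neuromodulation room at a designated time by a designated therapist".
- **Table 1** (section 2.1) groups the MADRS, PSS and PANAS under Assessment and schedules them at screening, in each of the three treatment weeks and at the 8-week follow-up. Section 3.1 makes the MADRS the primary outcome.
- **2.7 Blinding**, item (2): "A third-party evaluator will evaluate the treatment results without information regarding the subgroup". Item (1) adds that the person implementing the study does not know what stimulation modes A and B stand for.
- **2.6 Randomization and allocation concealment**: "The researchers will document the outcome measures objectively", and "The participants and researchers collecting maternal and infant clinical outcome data will also remain blind to the group distributions".
- **2.1 Study design**: "The research coordinator conducted a baseline visit before the start of the active study", and the baseline MADRS is gathered at that visit.
- **3.3 Follow up**: "The participants will be contacted by medical staff by phone or in person".

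No section names the MADRS rater for weeks 1 to 3 or for week 8, and nothing reconciles 2.11 with 2.7.

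**The concern.** As written, 2.11 merges two roles that 2.7 keeps apart: giving the stimulation and assessing the participant. The trial is described as double-blind, and its primary outcome is a depression score that leaves room for judgement if an observer scores it. An independent evaluator protects that score in a way that formal blinding of a therapist does not. Someone who attends sessions may form a view of the arm without being told it.

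The protocol gives grounds for this. Section 2.1 has those who run sessions record vital signs, session times and interruptions, and the abstract has side effects recorded at each treatment. Under 2.11.3 the sham current stops after the first minute, while active stimulation runs for 20 minutes. What a participant feels and reports can therefore differ by arm. If that view shifts the scoring, the shift goes directly into the estimated treatment effect. More participants would not remove it, and it cannot be repaired after the ratings are made.

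**Working it through.** **Step 1. Set the role assignments side by side.**

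| Task | Section | Assigned to |
|---|---|---|
| Stimulation sessions | 2.11.2 | a designated therapist |
| Treatment and assessments | 2.11 | the study's therapists |
| Evaluating treatment results | 2.7(2) | a third-party evaluator without group information |
| Documenting outcome measures | 2.6 | the researchers; collectors of clinical outcome data are blind |
| Baseline visit and baseline MADRS | 2.1 | the research coordinator |
| Follow-up contact | 3.3 | medical staff |

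**Step 2. Does 2.11 reach the primary outcome?** It does not name the MADRS. Table 1 uses Assessment as the heading over the MADRS, PSS and PANAS, so on the document's own usage it does. The PSS is called self-report in 3.2, and the PANAS is rated by the participant. The mode of the MADRS is not stated, so the point bears mainly on the MADRS and assumes that an observer scores it.

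**Step 3. Which rows conflict?** Rows 2 and 3 do. Anyone in the therapist role of 2.11 is part of the treating team and so not a third party. Row 4 conflicts with neither on blinding, but it does not say whether the researchers are the therapists or the evaluator. Row 5 conflicts with nothing: under 2.6 the baseline information is gathered before allocation. Row 6 assigns contact, not rating.

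**Step 4. What would a lean do to the error rate?** The protocol has no figure to reproduce here. The following is an illustration.

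- From the document: 79 analysed per arm and two-sided reading of alpha = 0.05 (section 2.5 gives the target number and alpha; two-sided is taken here).
- Assumed: SD of the MADRS comparison 8 to 10, no true effect, and a constant differential lean *b* between arms.

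SE = SD × √(2/79): 8 × 0.1591 = 1.27, and 10 × 0.1591 = 1.59.

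Rejection rate = P(Z > 1.96 − *b*/SE) + P(Z < −1.96 − *b*/SE).

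| Lean *b* | SD 8: *b*/SE | Rejection rate | SD 10: *b*/SE | Rejection rate |
|---|---|---|---|---|
| 1 point | 0.79 | 12.3% | 0.63 | 9.6% |
| 2 points | 1.57 | 34.9% | 1.26 | 24.2% |

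Only a lean that differs between arms has this effect. A lean common to both arms cancels in the difference.

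**The case against.** The best defence is that the protocol already blinds whoever collects outcomes. Section 2.6 says so directly, and 2.7(1) says that the implementer does not know what the modes stand for. On that view a therapist who rates is still a blinded rater. It can be added that 2.11 is a general sentence about standardising procedures, that 2.7 is the specific provision, and that a condensed article may leave rater scheduling to the full protocol.

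Much of this stands. The text shows an overlap of roles, not unblinding. But blindness to the allocation code is not the same as absence from the sessions, and the evaluator in 2.7 supplies the second protection. Nor is this an omission: the article says who assesses, and says it in two incompatible ways.

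A reader might infer more than the documents support:

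- **That the baseline and follow-up roles also contradict the others.** They do not, for the reasons in step 3. A different rater or contact mode that applies equally to both arms costs some precision but does not by itself bias the comparison.
- **That one therapist runs all 18 sessions and rates the same participant.** No section says this.
- **That the protocol concedes rater subjectivity.** The Discussion refers to subjective factors of patients, not of raters.
- **That sites may follow different sections.** The trial has a single centre; the risk is that its staff act on one section or the other.

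**Conclusion.** The contradiction between 2.11 and 2.7 is real and concerns the primary outcome. If 2.11 is followed, the separation of rater and treater is lost; if 2.7 is followed, it is kept. The documents do not say which governs.

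The possible size is material: the nominal 5% error would become roughly 10-12% with a 1-point differential lean and 24-35% with 2 points. These figures rest on an assumed SD, an assumed lean and observer scoring of the MADRS. They show what such a lean would cost, not that this protocol produces one. The point should be settled before MADRS ratings are collected after randomisation.

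**What to change.** 1. In 2.11, delete assessments from the tasks carried out by the treating therapists.
2. In 2.7 and 3.3, state that the third-party evaluator already named in 2.7 rates the MADRS at every post-randomisation time point, including week 8.
3. State in 2.7 that this evaluator does not deliver or attend sessions and does not see the session log.

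The baseline rating by the research coordinator can stay as it is, and no single contact mode needs to be imposed.

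Cost: a few sentences of protocol text and the scheduling of one rater, including the week-8 rating. No new role is needed.

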#### 2.11.1. Basic treatment

Patients with PPD will continue to receive clinical treatment and nursing care from their individual clinical programs throughout the trial. Their clinical treatment and nursing suppliers are will be blind to their group assignment. Clinical treatment and nursing care will not include the offer of antidepressants. If participants start taking antidepressants during the study, it will be recorded, and they will not be able to continue participating in the study. The record of antidepressants is shown in Table 2.

**Table 2 T2:** The records of patients with PPD taking antidepressants.

	**Antidepressants type**	**Dosage**	**Frequency**	**Dosing timepoint**
Patient				

#### 2.11.2. Active tDCS

Participants in the intervention group will receive active tDCS treatment for PPD. The anode of the electrode will be placed on the left dorsolateral prefrontal cortex (dlPFC), and the cathode on the upper edge of the right track. Based on a previous professional study, the current strength will be set at 2.0 mA (Vigod et al., 2019). The circular electrode area size will be set at 35 cm^2^ (5 × 7 cm). The duration of the treatment will be set at 20 min per session, once a day for 6 days each week (Figure 2A). The participants will be treated with tDCS only, and will not be simultaneously treated using other methodsI. The treatment will be performed in a neuromodulation room at a designated time by a designated therapist.

**Figure 2 F2:**
[figure not shown]
Current schematic diagram of active **(A)** and sham **(B)** tDCS. **(A)** The current rises and falls for 15 s, and lasts for 20 min. **(B)** The current rises and falls for 15 s and lasts for 1 min.

#### 2.11.3. Sham tDCS

in the control group will receive sham tDCS treatment. The anode of the electrode will be placed on the left dlPFC and the cathode on the upper edge of the right track. During the first minute, the current will be input every 30 s, after which there will be no current output throughout the remaining 19 min of the sham treatment (Figure 2B). The remaining parameters will be similar to those of the active group.

### 2.12. Study endpoints

The endpoints of this study are as follows:

(1) If a severe adverse reaction occurs during the intervention process, it will be terminated promptly to protect the participant.

(2) The intervention will be terminated if a serious complication or worsening situation occurs during the intervention.

(3) The intervention will be terminated if the participant requests to withdraw, does not accept the treatment, or does not cooperate.

(4) If the therapist repeatedly explains that the treatment approach is not working, the study will be suspended.

(5) The intervention will be terminated if the subjects have suicidal intentions, mental disorders, treatment for sudden mania, or acute maternity complications throughout and following treatment (as determined by the study team).

Participants will have autonomy over their involvement in the study and can discontinue at any stage. The researchers will record in detail the reasons why and when participants drop out of the study. Participants who discontinue the treatment early will be included in an intention-to-treat analysis, which can be used to obtain follow-up information if the participants are willing.

## 3. Outcome assessment

The main outcome measures for the study are feasibility, accessibility, and compliance with the trial protocol. Feasibility describes how well the trial protocol can be implemented. We record data on practicability related to eligibility (for example, the number of psychiatric visits and percentage of eligible postpartum psychiatric hospital patients), recruitment (such as the number of eligible patients, screening methods, reasons for non-involvement), and timing (including the time participants started treatment). We also ask patients with PPD whether they can distinguish which treatment (active tDCS or sham tDCS) they have received at the end of the procedure during the study period to assess the feasibility of our blinding methods. Accessibility refers to patients' satisfaction with and opinions on the intervention, focusing on maternal, neonatal, and infant outcomes, and on whether they experience any effects or adverse outcomes. Acceptability measures include participants' vital signs monitored during each session, the effects or adverse outcomes monitored at the end of each week of the study period, and questionnaires to assess maternal outcomes. Aiming to improve the precision of self-reported assessments of these health indices, we provide patients with PPD with a duplicate of the relevant questionnaire. Finally, we will take some measures to assess compliance, including the number of sessions attended during the overall and expected active study period, the number of patients who completed the 15 active study periods, the reasons for dropping out, and the proportion of follow-up data collection.

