Non-invasive brain stimulation (NIBS) is a non-traumatic, convenient, safe, and effective brain function therapy technique widely used in clinics. As a typical NIBS approach, transcranial direct current stimulation (tDCS) may be an effective brain stimulation medical technique with the potential to be an “optimal” treatment method for PPD. Additionally, tDCS, a local brain stimulation-based treatment approach, is dependent on the presence of abnormalities in the activity of the frontal lobe region of the brain, particularly the left and right dorsolateral prefrontal cortex (PFC) (George et al., 1997; Speer et al., 2000; Fitzgerald et al., 2003; Ardolino et al., 2005). In a meta-analysis of 10 studies, researchers found that, compared to sham tDCS, active tDCS was more favorable in alleviating symptoms of depression after 2 to 3 weeks of treatment (Kalu et al., 2012). Significantly, tDCS has proven to be safe in a wide range of trials. In one study involving the side effects of tDCS, 77 healthy controls and 25 patients with neurological diseases were examined 567 times, with the most prevalent side effects involving slight tingling, moderate fatigue, and mild tickling under the stimulation electrodes. After tDCS, approximately 10% of headaches and <3% of instances of insomnia and nausea were reported (Poreisz et al., 2007). Additionally, tDCS is an available treatment approach. The instrumentation required is cheap and mobile, and tDCS can be administered by trained technicians or by the individual themselves.

In summary, tDCS is a novel, safe, and non-pharmacological treatment technique for individuals suffering from PPD. The purpose of this protocol is to evaluate the efficacy and safety of tDCS as a method of treating PPD with a forward-looking, double-armed, sham-control, randomized controlled trial (RCT) protocol toP. This may be a guide to a larger multi-centered RCT that explicitly values the therapeutic effects of tDCS on the treatment of PPD. This study protocol may also be used to derive the initial impact dimensions for the sample size required to complete the most complete and reliable RCT.

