### 3.1. Primary outcomes

The primary outcome will be the severity of depression symptoms evaluated by the MADRS (Montgomery and Asberg, 1979), an item with 10 parts to evaluate depressive symptoms. It is one of the most extensively used tools for assessing the degree of PPD in clinical practice (Fernandes et al., 2019). Every item of the MADRS is scored on a seven-point scale (from 0 to 6). The higher the score, the more severe the depression, with a total score of 0–60. A total score of ≥35 indicates extreme depression, 30–34 indicates major depression, 22–29 indicates moderate depression, and 12–21 indicates mild depression (Hudgens et al., 2021).

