## 4. Discussion

tDCS is a novel, noninvasive therapeutic approach for treating PPD and has the potential to introduce a safe, effective, low-cost, and accessible method of treatment. The study protocol presented in this paper is a pilot RCT that aims to guide the development of a larger multi-center study on determining the efficacy and safety of tDCS as a treatment option for PPD. The main site of tDCS is located at the left dlPFC, as the prefrontal cortex (PFC) has extensive and close relationships with the center and the remaining regions of the brain. Additionally, the PFC plays a key role in organizing, guiding, regulating, and processing information received within the brain, thereby making the overall function of the central nervous system harmonious (Abdelnaim et al., 2020). Regarding the treatment of PPD, tDCS stimulates the dlPFC through anodic stimulation to enhance the excitability of this area and other cortical connections to regulate anxiety and depression. Another possible mechanism of action is related to neurotransmitters. A related study (Luscher et al., 2011) found that tDCS could significantly increase the levels of GABA, DA, and 5-HT, thereby decreasing the levels of depression. GABA is a major inhibitory neurotransmitter in the central nervous system. Alterations in GABA signaling are associated with severe depressive disorders (Kalueff and Nutt, 2007). Furthermore, the antidepressant effects of tDCS may occur through direct or indirect regulation of DRN 5-HT neurons. A study in 2020 established that an acute cathode of tDCS induces the activation of prolactin cortical neurons and the inhibition of DRN 5-HT neurons, the amplitude of which are higher than that of acute tDCS of the same intensity (Cambiaghi et al., 2020). All the mechanisms of tDCS make it an ideal therapeutic approach for treating PPD.

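### Sections 3 and 3.1 name different main outcomes and nothing ranks them; the compliance measure also counts 15 study periods where 18 sessions are scheduled

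*Protocol article*

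**What the plan says.** All references are to the protocol article.

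- **Section 3, opening:** "The main outcome measures for the study are feasibility, accessibility, and compliance with the trial protocol". Eligibility, recruitment, timing, satisfaction, adverse effects and attendance measures follow. None has a stated success criterion.
- **Section 3.1:** "The primary outcome will be the severity of depression symptoms evaluated by the MADRS". Section 3.2 lists only the PSS and PANAS as secondary.
- **Introduction:** "The purpose of this protocol is to evaluate the efficacy and safety of tDCS as a method of treating PPD".
- **Section 2.5:** a two-proportion formula with 5% type I error and 90% power gives 79 per group.
- **Section 4:** "The study protocol presented in this paper is a pilot RCT". Section 3.5 also calls it a pilot, and Section 2.9 states the aim as exploring whether a multi-centre trial is possible.
- **Session count:** within compliance, Section 3 counts "the number of patients who completed the 15 active study periods". Section 2.1 schedules "altogether 18 intervention or sham control sessions lasting for 20 min", and Section 2.11 says "The treatment will be administered six times per week for 3 weeks". The Abstract also gives 6 days per week for 3 weeks.

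**The concern.** The primary outcome decides what the trial can conclude. Here two neighbouring sections give that role to different things. One is a descriptive set about how well the trial runs; the other is a symptom score compared between arms. A reader of the results could not tell which of them the trial was meant to be judged on.

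If the choice stays open until the data are in, the emphasis can follow the result. A null MADRS comparison could be presented as a pilot that met its feasibility aims. A favourable one could be presented as the confirmatory result of a trial with 90% power.

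The session count is a smaller, separate matter. It sits inside compliance, which Section 3 treats as a main outcome, and the number of completers cannot be tabulated unambiguously while the course length is given as both 15 and 18.

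**Working it through.** **1. Does any section rank the two outcome sets?**

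| Section | What it contributes |
|---|---|
| 3, opening | Feasibility, accessibility and compliance are the main measures |
| 3.1 | MADRS severity is primary |
| 3.2 | PSS and PANAS are secondary; the feasibility set is not placed here |
| 2.12 (headed as endpoints) | Grounds for ending the intervention; no outcome hierarchy |
| 3.4 | Refers to primary and secondary outcomes without naming them |

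None does, so the conflict is between two positive statements. It is not a detail left out of a condensed article.

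**2. Does the sample size settle it?** Section 2.5 uses n = 2·p̄·q̄·(Zα + Zβ)² / (p1 − p2)².

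- *Dropout step, reproduced:* 2 × 79 = 158, and 158 / (1 − 0.20) = 197.5, rounded up to the stated 198. At 15% dropout it would be 158 / 0.85 = 185.9, or 186.
- *The 79, not reproducible from the article:* p1 and p2 are not given. As an assumption only, two-sided α = 0.05 and 90% power give (1.960 + 1.282)² ≈ 10.51. With 0.75 against 0.50, p̄ = 0.625 and n = 2 × 0.625 × 0.375 × 10.51 / 0.0625 = 78.8, which rounds up to 79. The pair 0.50 against 0.25 also gives 78.8. One-sided, 0.35 against 0.15 and 0.85 against 0.65 each give 80.3.
- *Reading:* the formula is for two proportions. Section 3.1 describes MADRS as a 0–60 score and defines no responder proportion, and Section 2.5 names no endpoint. The 79 therefore cannot be traced to MADRS or to a feasibility measure, and it does not resolve the conflict.

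**3. Session count.** The inputs are Section 2.1 (18), Section 2.11 and the Abstract (6 per week, 3 weeks), and Section 3 (15).

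- 6 × 3 = 18, which reproduces Section 2.1.
- 18 − 15 = 3, and 3 / 18 = 16.7%. Equivalently, 15 / 18 = 83.3%.
- 15 would follow from 5 × 3, but no section gives five sessions per week.

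**The case against.** The strongest reply on the outcomes is that the hierarchy is clear enough in practice. Only Section 3.1 is headed as primary, it names one instrument, and Section 3.2 follows with the secondaries. The feasibility items are descriptive and carry no hypothesis test. That makes MADRS the more natural primary and supports the direction of the fix. It does not remove the Section 3 sentence that says otherwise, and the pilot language in Sections 3.5 and 4 gives that sentence weight.

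On the session count, the reply is that the same sentence in Section 3 also records how many sessions were attended, so a shortfall would be visible. That stands, and it limits the harm. The two figures still disagree.

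Three stronger readings are tempting, and the article does not support them:

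- *A participant who misses three sessions is recorded as a completer.* No section makes 15 a threshold that can be met early within an 18-session course. The wording reads more like a wrong total for the whole course.
- *The 15 enters the per-protocol set.* Section 3.4 plans a per-protocol analysis but ties it to no session count. The definition may sit in a fuller document, so this effect is possible but not shown.
- *The 5% and 90% already belong to MADRS, so making it primary would match Section 2.5.* Section 2.5 names no endpoint, and it describes the study as preliminary, not as a pilot.

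**Conclusion.** Both contradictions stand in the current text. The first matters more: feasibility, accessibility and compliance are the main outcomes in Section 3, MADRS severity is primary in Section 3.1, and nothing ranks them. Its consequence cannot be expressed as a number. It is that the article leaves open which result the trial is to be judged on.

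The second is a discrepancy of 3 sessions, 15 against 18, or 17% of the schedule in Sections 2.1 and 2.11. That percentage takes 18 only as the reference for measuring the gap; no view is taken on which figure is right.

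Preferring MADRS rests on the Section 3.1 heading, the efficacy purpose in the Introduction and the between-group tests planned in Section 3.4. It does not rest on the sample size.

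**What to change.** 1. Amend the opening of Section 3 so that MADRS, as in Section 3.1, is the single primary outcome, consistent with the purpose in the Introduction. List feasibility, acceptability and compliance as descriptive secondary outcomes.
2. Reconcile the 15 in Section 3 with the 18-session schedule in Sections 2.1 and 2.11, and count completion on the reconciled number.

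The cost is protocol wording, ideally settled before any unblinded analysis. The feasibility and attendance data are still collected, and no procedure changes. The amendment should not say that the 90% power in Section 2.5 now applies to MADRS; that would need the endpoint and the two assumed proportions behind the 79 to be stated.
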